### Sample Size and Power Calculations

350 women choosing a levonorgestrel-releasing IUC (LNG-IUC, "Mirena^®^", Bayer Inc, Canada), and 366 women choosing a "T" shaped copper IUC with 380 mm^2 ^surface area of copper including copper bands on the "T" arms (CuT380-IUC, "Flexi-T380(+)^®^", Prosan, The Netherlands) will be recruited and randomly allocated to each of two treatment arms: immediate insertion (experimental intervention) vs. planned delayed insertion (recommended care), representing a total enrollment of 716 women into this Phase IIIb RCT (See Table 1). This sample size will provide 90% power in the levonorgestrel stratum to distinguish predicted one year pregnancy rates of 1.2% (immediate) versus 8.7% (delayed) and 80% power for corresponding detection of 2.7% and 9.7% in the copper device users.

**Table 1 T1:** Enrollment Allocation

	Immediate	Delayed	Total
LNG-IUC	175	175	350

CuT380-IUC	183	183	366

Total	358	358	716

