### Operational definition for outcome

Although our outcome of one year pregnancy rate is conceptually simple, exact determination of conception dates is clearly infeasible. Consequently our actual outcome definition provides a pragmatic approximation based on the varying exactitude of imputations based on provincial Medical Service Plan billings related to abortions, miscarriages, still births and live births. Subsequent abortions performed within our study clinics for enrolled participants will be noted along with specific clinical information on pregnancy duration. For abortions performed elsewhere such as those for BC university students studying out of province, or those performed by individual physicians at rural or remote hospitals within BC, exact gestation may not be available. In the BC health administrative databases abortions are billed as under 7 weeks for medical abortions, and as under 14 weeks, 14 weeks to under 18 weeks, and 18 weeks and over for surgical abortions. Miscarriages by definition occur anytime under 20 weeks or are classed as still birth when over 20 weeks of gestation. Thus for subsequent pregnancies where the specific gestation is unknown, we will consider a pregnancy to have occurred in the first year according to the following conservative adjustments to one year follow-up dates. (see Table 3.)

**Table 3 T3:** Operational definition of a pregnancy as derived from administrative billing data

Billing Type	Nominal weeks of gestation	Cut-off for operational definition
Abortion (medical)	< 7 weeks*	1 year + 4 weeks
Abortion (surgical)	< 14 weeks	1 year + 6 weeks
Abortion (surgical)	14-18 weeks	1 year + 13 weeks
Abortion (surgical)	≥ 18 weeks	1 year + 17 weeks
Miscarriage	< 20 weeks	1 year + 11 weeks
Still birth	≥ 20 weeks	1 year + 25 weeks
Live birth	Birth date - GA	1 year + XX*

*In Canada, mifepristone is not available. Medication-induced abortions using methotrexate and misoprostol are offered in British Columbia up to a maximum of 49 days (7 weeks) from last menstrual period.

** Where XX = median conceptual age for live births in BC

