### Analysis methods

We will compare one year pregnancy rates using a chi-squared test declaring significance if p < .05 and provide 95% confidence intervals for the difference in pregnancy rates using the large sample normal approximation for differences in proportions. This simple approach is valid so long as no systematic difference in follow-up occurs between groups. As a check, we will also conduct analysis to account for partial follow-up. Since our outcome definition is essentially composite and the relevant risk periods differ by components, Kaplan-Meier estimates for each component event will be determined and composite estimates will be obtained by summing the estimated cumulative event rates (calculated as 1 - the survival function) at the time-points indicated in our operational definitions. Confidence intervals around the difference in these estimates will be calculated using the bootstrap.

Rates for all secondary outcomes will be calculated for events occurring within one year following abortion, and annually for five years, using the follow-up questionnaires, direct access to clinical follow up visit records, and billing and procedure coding data from the administrative health system databases. Multivariate logistic regression will be used to examine demographic, socioeconomic, and obstetrical factors in relationship to primary and secondary objectives.

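### The partial-follow-up check sums 1 minus Kaplan-Meier over competing pregnancy outcomes, so it slightly overstates the delayed arm's pregnancy rate unless a risk-set rule the article does not state is applied (minor)

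*Protocol article*

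**What the plan says.** In Analysis methods, the primary comparison of one-year pregnancy rates is a "chi-squared test declaring significance if p < .05", with a normal-approximation interval for the difference. The section says this is valid only if follow-up does not differ systematically between groups, and adds: "As a check, we will also conduct analysis to account for partial follow-up".

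The method for that check is then stated. One curve is fitted per type of outcome, on the ground that "the relevant risk periods differ by components". The way the curves are combined is also fixed: "composite estimates will be obtained by summing the estimated cumulative event rates (calculated as 1 - the survival function"). Each curve is read at its own operational cut-off, and the interval for the difference comes from the bootstrap.

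The components are given in Operational definition for outcome: "billings related to abortions, miscarriages, still births and live births". Table 3 splits these into seven rows. Its column "Cut-off for operational definition" runs from one year plus 4 weeks to one year plus 25 weeks, with an unspecified XX for live birth.

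The article does not say whether a woman leaves the risk set for one component when she has another, or whether only her first later pregnancy counts.

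**The concern.** The components are alternative ends of the same pregnancy. A woman whose first later pregnancy ends in abortion cannot have that pregnancy end in birth. There are two ordinary ways to run the stated method:

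- **Censor at any other outcome.** Each 1 - KM then estimates the risk in a setting where the other outcomes cannot occur. The sum exceeds the probability of any pregnancy.
- **Keep women at risk and count later pregnancies of another type.** A woman with an early abortion and a later birth, both inside their cut-offs, adds to two components. The Analysis section keeps women in the trial after a later abortion or delivery, so this can happen.

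The absolute excess grows roughly with the square of the risk, so it falls almost wholly on the delayed arm and widens the difference.

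What is at stake is the usefulness of the check. It is the only analysis the article offers for partial follow-up. A departure from the primary result would be read as a sign of attrition bias, when part or all of it could come from the estimator.

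**Working it through.** **1. The plan's own figures reproduce.** Inputs from Estimation of Probable Rates of Pregnancy: device failure 0.1% (LNG) and 1.7% (copper), expulsion 0.05, pregnancy risk without a device 0.24, return 65%, loss up to 5%. The displayed formulas are not in the text available, so they are inferred from these inputs.

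- LNG immediate: 0.95 × 0.001 + 0.05 × 0.24 = 0.01295. Delayed: 0.65 × 0.01295 + 0.35 × 0.24 = 0.0924. Times 0.95: 0.0123 and 0.0878 (article: .012 and .0874).
- Copper immediate: 0.95 × 0.017 + 0.05 × 0.24 = 0.02815. Delayed: 0.65 × 0.02815 + 0.35 × 0.24 = 0.1023. Times 0.95: 0.0267 and 0.0972 (article: .027 and .097).

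The plan claims "90% power in the levonorgestrel stratum to distinguish predicted one year pregnancy rates of 1.2% (immediate) versus 8.7% (delayed"). A two-sided 0.05 test with pooled variance gives 90.2% with 175 per arm. For copper (183 per arm, 2.7% v 9.7%) it gives 79.5%, against the stated 80%.

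**2. Closed form, other outcomes censored.** Assume K equal components and a common horizon. With true risk p, let H = -ln(1 - p). Each component gives 1 - exp(-H/K), so the sum is K(1 - exp(-H/K)), with upper limit H. The excess over p is approximately (H²/2)(1 - 1/K). With K = 7, as in Table 3:

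| | Immediate | Delayed | Difference | Excess |
|---|---|---|---|---|
| LNG, true | 1.20% | 8.70% | 7.50 | |
| LNG, summed | 1.21% | 9.04% | 7.84 | +0.34 (4.5%) |
| Copper, true | 2.70% | 9.70% | 7.00 | |
| Copper, summed | 2.73% | 10.13% | 7.40 | +0.40 (5.7%) |

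For LNG delayed, H = -ln(0.913) = 0.0910, and 7 × (1 - exp(-0.0910/7)) = 0.0904. With K = 2 the excess in the difference is +0.19 (LNG) and +0.23 (copper). At the upper limit it is +0.40 and +0.47.

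**3. Simulation with the Table 3 horizons.** 2 million women per arm, 65% return and about 5% loss by one year. The outcome mixes, gestational ages and an XX of 38 weeks are assumptions. Differences (delayed minus immediate) in percentage points:

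| | Aalen-Johansen sum | Summed 1 - KM, censored | Summed 1 - KM, later pregnancies counted |
|---|---|---|---|
| LNG, birth-heavy mix | 7.93 | 8.25 (+0.33) | 8.20 (+0.28) |
| Copper, abortion-heavy mix | 7.26 | 7.61 (+0.35) | 7.56 (+0.30) |
| Copper, birth-heavy mix | 7.47 | 7.85 (+0.39) | 7.75 (+0.29) |

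By arm, in the LNG row with censoring: immediate 1.31% v 1.30%, delayed 9.56% v 9.23%. The Aalen-Johansen sum matched the direct count of first qualifying events within 0.02 points in every scenario.

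**4. Low return.** The article also cites a 26% return rate. There the excess in the difference is about 1.25 to 1.4 points if other outcomes are censored, and about 0.6 if they are not.

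**5. Against what the check is meant to detect.** With no loss at all, a 50/35/15 mix of abortion, birth and miscarriage, and censoring, the simulated difference moves from 7.94 to 8.24 (LNG, +0.30) and from 7.46 to 7.82 (copper, +0.35 before rounding). The planned 5% loss shrinks the difference by 0.05 × (9.24 - 1.30) = 0.40 (LNG) and 0.05 × (10.23 - 2.82) = 0.37 (copper). The artefact is therefore about 75% (0.30/0.40) to 95% (0.35/0.37) of that effect, and it points the way a correction for lost pregnancies would.

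**6. Against the trial's precision.** The 95% half-width is 1.96 × √(0.012 × 0.988/175 + 0.087 × 0.913/175) = 4.5 points for LNG, and likewise 4.9 for copper. At 65% return the artefact is under a tenth of either.

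**The case against.** The strongest reply is that the article does not fix the reading that fails. If only first pregnancies count, and women with another outcome stay in the risk set until their own potential end of follow-up, the summed curves are unbiased. A condensed article may leave such rules to the full protocol or SAP. This stands in part. A reader might infer that the sum is wrong however it is run, and that is too strong. But the article does state the estimator, and neither condition needed to make it valid appears. Censoring at other outcomes is the ordinary implementation.

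A second reply is that the check does not become more likely to support immediate insertion. This stands. A reader might infer that the inflated difference would tend to confirm a benefit, but the interval widens too. Simulated at the planned sizes, with first events only and censoring, the LNG difference was 7.73 v 7.49 points with SD 2.38 v 2.27 (mean/SD 3.24 v 3.30, from unrounded values). Copper was 7.27 v 6.99 with SD 2.63 v 2.50 (2.77 v 2.80). With equal true rates in both arms the bias in the difference is nil.

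A third reply is that the size is trivial beside sampling error, and that provincial database linkage should keep loss low. Both are true. Low loss does not remove the artefact, however, because it is present with no loss at all.

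**Conclusion.** The point holds as a minor one. The check, as worded, is not a sound estimate of the one-year pregnancy proportion unless an unstated first-pregnancy and risk-set rule is applied. Under either ordinary implementation at the planned rates, the delayed arm is about 0.3 to 0.4 points too high, the immediate arm is almost unchanged, and the difference is about 4 to 5% too large in most runs. If return falls to 26% and other outcomes are censored, the difference is about 1.3 points too large.

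The sizes rest on an assumed outcome mix, gestational ages, live-birth offset and loss pattern. Two mixes and the closed form agree on direction and order of size.

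Two wider inferences are not supported. The trial's primary effect is not inflated: the chi-squared comparison, its interval, the sample size and the power do not use this estimator. Nor does the article carry the summed curves to the five-year pregnancy rates: it reads them at the Table 3 time-points, which are one-year cut-offs.

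**What to change.** In Analysis methods, replace the summed 1 - KM rule as follows:

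- Define the event as each woman's first qualifying pregnancy outcome after enrolment.
- Estimate each component by its Aalen-Johansen cumulative incidence, with the other outcomes as competing events.
- Read each component at its Table 3 cut-off and sum them.
- Keep the bootstrap interval for the difference.

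The cost is one or two sentences and a standard software routine. No new data are needed, and nothing changes in the primary analysis or the sample size. If the full protocol or SAP already counts first pregnancies only and keeps women with other outcomes in the risk set, it is enough to say so here.

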### Survey Analysis

The quantitative data from the CSQ will be analyzed using descriptive statistics. The CSQ contain several scales providing composite scores that can be used to indicate differences in the secondary outcomes. Open ended questions will be analyzed through content analysis focusing on key topics.

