### Enrollment process

All women presenting to a participating clinic for an abortion of a pregnancy over 12 weeks and under 24 completed weeks receive information on the research study web page [35] at the time they book their appointment, and a study information brochure upon check in. Women consenting to participate complete an initial CSQ. Participants receive their chosen IUC at no cost in addition to a gift card and are randomly allocated using an internet-based randomization service [36], to immediate or planned delayed insertion, with stratification for device, parity and clinic site. This trial has been registered at controlled-trials.com (ISRCTN19506752). A pilot phase study undertook to develop, pilot test and focus group review the CSQ from an existing validated questionnaire [37], adapted for use in our population and for this study, including translation into the three most common non-English languages in our population (Cantonese, Mandarin and Punjabi). A user-friendly internet based format for each of the four languages and sampling times (intake, three, six and 12 month and annually to five years) was implemented.

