### Outcome determination

CSQ are offered by mail, email or as a web-based questionnaire at 3, 6 and 12 months and annually to five years following enrollment. The CSQ collect data on expulsion of IUC, effectiveness and satisfaction with contraceptive method and insertion timing assigned, any removal of the IUC, any change to contraceptive method or intention to conceive, any interval pregnancies and their outcomes, and any adverse events. In addition participants are asked to arrange to return to any of the study sites or see their primary health care provider for a follow-up clinical examination at 3, 6 and 12 months following the abortion. Information from clinical visits and CSQ will be used in conjunction with BC administrative health database information to determine outcomes.

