### Analysis

*Primary outcome *will be examined in an intention-to-treat framework as pregnancy rate at one year among women randomized to immediate insertion compared to women randomized to a planned insertion at 4 weeks ("delayed insertion") for each of the two IUC devices. For example, if women in the delayed group present for insertion after the specified 4+/-1 week insertion window, or even at the time of a subsequent abortion or delivery, we will insert the device at the women's request and her assignment for the primary analysis will not change. Similarly if for any reason a woman assigned to the immediate insertion group is unable to have her insertion immediately (for example, should she have an unattended expulsion/delivery of her pregnancy prior to the planned surgical abortion) then insertion will be offered at the time the woman and her physician would normally undertake to do so, and whether or not her insertion ever occurs, her assignment for the purpose of analysis will not change. Thus our primary outcome of pregnancy rate at one year reflects real life conditions.

*Secondary outcomes *include: costs and cost effectiveness, cumulative annual pregnancy rate, device insertion rate, loss to follow-up; continuation of method; adverse events (such as infection or perforation); expulsion; outcomes among those participants who were chlamydia positive at the time of insertion; satisfaction with IUC chosen and with insertion timing assigned. These outcomes will be assessed initially at one year, then annually through the five year device effectiveness period.

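### The questionnaire scores are meant to indicate differences in satisfaction, but the stated analysis is descriptive, with no estimate or interval for the arm difference and no use of the repeated waves

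*Protocol article*

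**What the plan says.** All references are to the protocol article.

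- **Survey Analysis** names the method for the questionnaire (CSQ): "The quantitative data from the CSQ will be analyzed using descriptive statistics". It then gives the purpose of the scales: "The CSQ contain several scales providing composite scores that can be used to indicate differences in the secondary outcomes". Open questions go to content analysis.
- **Analysis** lists among the secondary outcomes "satisfaction with IUC chosen and with insertion timing assigned".
- **Enrollment process** describes a web format for each language and for the "sampling times (intake, three, six and 12 month and annually to five years) was implemented". It also says: "Women consenting to participate complete an initial CSQ". Randomization is stratified by device, parity and clinic.
- **Outcome determination** says what the follow-up forms collect, including "effectiveness and satisfaction with contraceptive method and insertion timing assigned".
- **Analysis methods** says of the secondary outcomes: "Rates for all secondary outcomes will be calculated for events occurring within one year following abortion, and annually for five years". It adds a multivariate logistic regression on characteristics of the women.

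**The concern.** The stated method and the stated purpose do not meet. Descriptive statistics summarise the scores in each arm at each wave. They do not by themselves say how far an observed gap between arms could be sampling noise. Elsewhere the article does name inferential methods: a chi-squared test, a 95% interval and a bootstrap interval for pregnancy (Analysis methods), and bootstrap intervals for mean costs and benefits (Health Economic Analysis). The scale scores get none of these.

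The second part is the repeated measurement. Each form is a separate occasion on which a woman may or may not respond, and the Introduction describes this population as one with poor adherence to follow-up after abortion. Database linkage is the protocol's answer for pregnancy, but a linked billing record cannot supply a satisfaction score. Wave-by-wave summaries therefore describe whoever responded at that wave, and they ignore what earlier forms say about women who have since stopped responding.

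At stake is the reading of a named secondary outcome: a difference in mean satisfaction could be taken as real, or as absent, with no stated measure of its uncertainty.

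**Working it through.** **Is the arm difference covered elsewhere?** The passages set side by side:

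1. Survey Analysis: descriptive statistics for the quantitative questionnaire data. No test, model or interval is named.
2. Analysis methods, rates for secondary outcomes: these are rates of events in a period. A composite scale score is not an event.
3. Analysis methods, logistic regression: the factors named are participant characteristics. Randomized arm is not among them, and a scale score would first have to be dichotomised.
4. Analysis methods, check for partial follow-up: defined for the pregnancy outcome through its component events. No counterpart is stated for scores.

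So no section states an estimate with an interval for the arm difference in a scale score.

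**How large is the unstated sampling error?** The article gives no SD, response rate or expected difference for any scale, so there is no figure of its own to reproduce. The calculation is in SD units.

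- Inputs from Table 1: 175 women per arm (levonorgestrel), 183 per arm (copper), 358 per arm (both). These sizes were set for the pregnancy rate.
- Assumptions: equal SD in the two arms, and questionnaire response of 100% or 60%. The 5% loss allowed for under Estimation of Probable Rates of Pregnancy concerns pregnancy, not questionnaire return.
- Formula: 95% half-width = 1.96 × √(2/n), with n respondents per arm.

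Full response:
- Levonorgestrel: 1.96 × √(2/175) = 0.21 SD
- Copper: 1.96 × √(2/183) = 0.205 SD
- Pooled: 1.96 × √(2/358) = 0.146 SD

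Assumed 60% response (n = 105, 109.8 and 214.8 per arm):
- Levonorgestrel: 1.96 × √(2/105) = 0.27 SD
- Copper: 1.96 × √(2/109.8) = 0.265 SD
- Pooled: 1.96 × √(2/214.8) = 0.19 SD

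Within a device stratum, then, a gap of about 0.2 SD between two bare means is compatible with no difference even if every woman responds.

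**Can the intake score be used?** Satisfaction with the timing assigned cannot exist before allocation, and satisfaction with the study device cannot exist before insertion. The article shows an intake questionnaire but does not show that it carries the same scales. For the satisfaction outcomes named, the usable repeated data are therefore the follow-up waves.

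**The case against.** The strongest reply is that Survey Analysis is three sentences in an article that condenses a fuller protocol, and that the model and interval for a secondary scale normally sit in an analysis plan, which is not shown here. The text is also soft: the scores can be used to indicate differences, not that they will be. The Analysis section spells out the arm comparison for the primary outcome and only lists the secondary ones. This stands as far as missing detail goes, and an unseen plan may add an interval. It does not fully answer the point, because the section is not silent. It names a method, and that method falls short of the use given to the scores in the next sentence.

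A reader might infer four stronger claims, and the article does not support them:

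- *Description is the sole analysis and no valid comparison can result.* The text does not say only, and it does not exclude intervals. Means, SDs and counts by arm would let a reader build an interval at each wave.
- *The plan throws away a gain from baseline adjustment.* With an assumed intake to follow-up correlation of 0.3 to 0.5, the variance factor 1 − r² would be 0.91 to 0.75. No matching intake scale is shown, and for the satisfaction items named none can exist, so no such gain can be claimed.
- *Non-response will bias the arms differently.* This is possible, since women know their timing, but the article gives no questionnaire response rate and no difference between arms.
- *A mixed model would cure missing forms.* It helps only if missingness depends on observed data, and it adds nothing for women who return no form.

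**Conclusion.** The point holds in a limited form. The article states a descriptive analysis for scores that it also relies on to indicate differences in secondary outcomes. No estimate or interval for the arm difference is stated, and the repeated waves are not used together. The size is the sampling error left unreported: roughly 0.15 SD (pooled) to 0.21 SD (levonorgestrel) at full response, and 0.19 to 0.27 SD at 60% response. These figures rest on equal SDs and on response rates that are assumptions here. The first follows from Table 1 numbers alone, and the second shows how quickly it widens. No bias is demonstrated. This is a worthwhile, inexpensive improvement to a secondary analysis, not a defect in the trial's main comparison.

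**What to change.** Reword Survey Analysis along these lines: for each composite score, the difference between immediate and delayed insertion at 12 months will be estimated with a 95% confidence interval from a repeated-measures model over the follow-up waves (3, 6 and 12 months, with annual waves added as they accrue). The model will include all randomized women who return at least one follow-up form, with terms for arm, wave and arm by wave, adjusted for parity, clinic and device. Results will be shown by device, in line with the primary analysis. The intake score will be a covariate only for scales measured at intake. The number of forms returned at each wave will be tabulated by arm.

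Keep descriptive tables for single items and content analysis for open questions.

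The cost is one additional model per scale and a stated reliance on missing-at-random. No new data are needed.
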